## Abstract

**Introduction::**

Fingertip amputation injuries are common in all ages. Conservatively treated fingertips can regenerate skin and soft tissues to form a functionally and cosmetically excellent new fingertip. Little is known about this ability that, in humans, is confined to the fingertips. Even less is known about the role of the bacteria that regularly colonize these wounds without negative impact on regeneration and healing.

As an alternative to surgery, self-adhesive film dressings are commonly used to establish a wet chamber around the injury. These dressings leak malodorous wound fluid eventually until the wound is dry. Having that into consideration, we have therefore developed a silicone finger cap that forms a mechanically protected, wet chamber around the injury for optimal regeneration conditions. It contains a puncturable reservoir for excess wound fluid, which can be thus routinely analyzed for diagnostic and research purposes.

This study protocol explains the first randomized controlled trial (RCT) on the semiocclusive treatment of fingertip amputations in both children and adults comparing traditional film dressings with the novel silicone finger cap. Being the first RCT using 2 medical devices not yet certified for this indication, it will gather valuable information for the understanding of fingertip regeneration and the design of future definitive studies.

**Methods and analysis::**

By employing an innovative pseudo-cross-over-design with a dichotomous primary endpoint based on patients preference, this pilot study will gain statistically significant data with a very limited sample size. Our RCT will investigate acceptance, safety, effectiveness, and efficacy of this novel medical device while gathering information on the clinical course and outcome of conservatively treated fingertip injuries. A total of 22 patients older than 2 years will be randomly assigned to start the conservative treatment with either the traditional film-dressing or the novel finger cap. The treatment will be changed to the other alternative for another 2 weeks before the patient or the guardian is confronted with the decision of which method they would prefer for the rest of the treatment (if required).

**Ethics and dissemination::**

Ethical approval (EK 148042015) of the study protocol has been obtained from Institutional Review Board at the TU Dresden. The trial is registered at the European Database on Medical Devices (EUDAMED-No.: CIV-15-03-013246) and at ClinicalTrials.gov (NCT03089060).

## Introduction

1

Fingertip injuries are very common. In pediatric emergency departments, fingertip injuries account for up to 2%^[1]^ of appearances of children under 14 years of age with 25% of these injuries being more serious, needing surgical treatment, in 15% of the cases under general anesthetics.^[1]^

Already in 1974, Illingworth reported on pediatric fingertip injuries with substance loss, that were treated conservatively with very good success.^[2]^ The superiority of the conservative approach was afterwards demonstrated in comparative studies.^[2–5]^ Later, sulphadiazine gloves, and thus a method of occlusive dressing that formed a wet chamber around the injury, were used.^[6]^ Söderberg et al^[7]^ used ink tattoos on the wound edge to show that human fingertips regenerate de novo under conservative treatment. Additionally, the use of film dressings to occlude the injured fingertips was demonstrated in a series of 200 patients in 1993.^[8]^ The authors concluded that this kind of treatment should be recommended for all fingertip injuries.^[8]^

Surgical approaches for fingertip amputation injuries that cannot be subjected to primary closure include stump plasties, local, or distant flaps (eg, V-Y-plasty, etc), microsurgical replantation, composite grafts, or skin transplants.^[9]^ There are only little and conflicting data on the indication of conservative versus surgical techniques. Controversies also exist on necessary wound disinfection, if exposed bone should be shortened before any occlusive dressing is applied and, whether or not, amputates should be reattached as composite grafts.^[10–12]^

In many centers the conservative management of fingertip injuries is accomplished with self-adhesive film dressings.^[8,13]^ However, this management is sometimes difficult, especially since these dressings do not stick to wet skin. Conventional dressings do not form a protected chamber around the wound, additional splinting is often needed^[5,6]^ and leakage of malodorous wound fluid is very disturbing. Therefore, we have optimized the conventional occlusive dressings by applying techniques known from silicone finger ortheses and designed a novel silicone finger cap that deals with the aforementioned issues.

This novel silicone finger cap is now evaluated for the first time in an investigator initiated, randomized controlled clinical trial regarding the acceptance of the finger cap in comparison to conventional film dressings using a pseudo-cross-over study design. As both medical devices are not certified for the treatment of deeper wounds and exposed bone, this randomized controlled trial (RCT) is a pilot study by definition. By employing a pseudo-cross-over-design with a summative dichotomous primary end-point (patient preference) we will gain statistically significant data despite the limited sample size while gathering important data with a variety of secondary end-points to plan for future definitive studies and better understand fingertip regeneration.

As well as evaluating the safety and efficacy of this novel treatment, secondary endpoints of our study include clinical, functional, microbiological, and quality-of-life parameters. Additionally, our RCT includes a substudy for the harvesting of wound fluids from the puncturable reservoir incorporated in our finger cap. This will allow the search for human and bacterial soluble factors that may promote tissue regeneration and limit bacterial growth to local colonization. Our study starts enrolling patients in August 2017.

## Methods and analysis

2

### Study design

2.1

This pilot study is a monocentric, prospective, randomized, controlled clinical trial. Primarily, it will investigate the acceptance of the silicone finger cap in comparison to conventional film dressings. Using sealed neutral envelopes prepared by external staff from the Coordinating Centre for Clinical Trials, our patients will be randomly assigned by the study doctors to begin their treatment either with the finger cap or the film dressing. After 2 weeks they will be changed to the other treatment modality. After another 2 weeks have passed, patients/guardians will have to decide prior to the dressing change which treatment they would like to receive thereafter if further occlusion is needed. The primary clinical endpoint of this pseudo-cross-over study (Fig. 1) is the rate of patients/guardians who decide to continue their treatment with the silicone finger cap. Further secondary endpoints include the determination of the safety of the finger cap in comparison to the film dressing and the determination of disease-specific quality of life during the treatment with the silicone finger cap in comparison to the film dressing using a modified quality of life Wuerzburg Wound Score regarding pain during application and treatment with the finger cap, restrictions in daily activities and quality of life.^[14]^ Also the necessity of unplanned dressing changes in comparison to the film dressing and changes in microbiological colonization in the wound during the treatment will be registered. Additionally, we will measure the reepithelialization rate and determine the tissue growth at 28 days and at 4 months after the injury. We will also test the function of the regenerated perspiratory glands and the clinical outcome in terms of sensitivity and motility of the injured fingertip as well as cosmetic aspects.

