On day 14 after the injury, the occlusive dressing method is changed. Patients treated with the conventional film dressing get a silicone finger cap and vice versa. Further 14 days later the patient decides which dressing she or he respectively the guardians would prefer for the remaining treatment if needed before the dressing is removed. The chosen treatment is then applied if further treatment is needed. At day 42 after the injury the treatment of the wound is orderly finished and the wound should be reepithelialized. The occlusive dressing is removed and photographs of the injury site are taken. If the wound is not fully epithelialized at this point, a conventional film dressing is used as long as further occlusion is needed. Final follow-up examination takes place 4 months after the injury. At the follow-up we test the function of the perspiratory glands and the regeneration of the fingerprint using Moberg Ninhydrin test.^[19]^ Also the range of motion in the distal interphalangeal, proximal interphalangeal and metacarpophalangeal joints, and the 2-point-discrimination threshold in the area of the injury is checked in comparison to the corresponding finger of the contralateral hand.^[20]^ Moreover, we also measure the soft tissue thickness above the bone in the region of the healed injury using medical ultrasound. Finally, patients have to complete a follow-up questionnaire. At each visit the dressing or, when applicable, the exposed finger is photographed from all perspectives. High definition photographs will be digitally analyzed and kept for documentation purposes. In this study, we will introduce a new volume-rendering method for monitoring finger growth 3-dimensionally. Photographs will be rendered in 3-dimensional models and advanced 3-dimensional segmentation, and filtering algorithms will be used to measure volume progress of the injured finger. This method will allow monitoring of tissue recovery in micrometers quality.

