#### Proposed sample size

2.6.1

There is no certified medical device available for the conservative management of fingertip amputation injuries. Opsite Flexigrid (Smith & Nephew Medical Limited, Hull, England) has not been certified for full thickness amputations injuries as described, and our novel finger cap has never been used before in a controlled trial. Therefore, this study is per definition a pilot study that has to be limited to a small sample size in order to comply to German and European legislation as well as to guidelines of good clinical practice.

The primary objective is the rate of patients who decide for the silicone finger cap at day 28. At this point they have experienced both methods (conventional film dressings and silicone finger cap) for 2 weeks each. This rate can be regarded as a measure of the acceptance of the silicone finger cap. If 80% of the patients in this study decide for the silicone finger cap we consider the hypothesized superiority of the finger cap as verified. Assuming that approximately 80% of the patients decide for the silicone finger cap, 20 patients (95% confidence interval, one-sided, 65% lower limit, the distance from the rate to the lower limit of the confidence interval is at most 15%) are needed (Program nQuery-Advisor 6.01, Copyright^©^ 1995–2005, Janet D Elashoff). When considering 2 possible drop-outs, 22 patients must be included.

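### At 28 days and 4 months, healing outcomes compare device order rather than cap with film, so they do not support the efficacy wording

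*Protocol article*

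**What the plan says.** **What is randomised.** Section 2.1: "our patients will be randomly assigned by the study doctors to begin their treatment either with the finger cap or the film dressing". Randomisation therefore fixes the order of the two devices.

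**When devices change.** Section 2.1: "After 2 weeks they will be changed to the other treatment modality". Section 2.5 gives the day: "On day 14 after the injury, the occlusive dressing method is changed". Section 2.6.1 describes the position at day 28: "At this point they have experienced both methods (conventional film dressings and silicone finger cap) for 2 weeks each". After that the patient or guardian chooses: "The chosen treatment is then applied if further treatment is needed". A wound still open at day 42 gets film, whatever was worn before (section 2.5).

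**When healing is measured.** Section 2.1: "we will measure the reepithelialization rate and determine the tissue growth at 28 days and at 4 months after the injury". Section 2.5 places sweat-gland function, joint motion, two-point discrimination and soft-tissue thickness at the 4-month visit. No healing endpoint is named at day 14.

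**What is claimed.** The abstract (Methods and analysis): "Our RCT will investigate acceptance, safety, effectiveness, and efficacy of this novel medical device". The Introduction repeats the claim for safety and efficacy.

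**How secondary endpoints are analysed.** Section 2.8 makes them exploratory. It lists two-sample tests (t, U, chi-square) and paired tests (paired t, Wilcoxon) without assigning them to endpoints.

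**The concern.** A comparison of randomised groups isolates a device effect only while the groups differ by device. For healing that is the first fortnight. From day 14 each group receives what the other had, and a wound does not return to its starting state at the exchange. A day-28 measurement therefore carries the results of both fortnights. By 4 months it also carries a device chosen by the patient and, for slow healers, a further spell of film.

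A two-sample test on healing at 28 days or 4 months would look like cap against film but would compare cap-then-film with film-then-cap. The Introduction says the secondary data are meant to help plan definitive studies. A null or reversed healing signal that comes from the design could be carried into that planning as evidence about the cap. A larger sample would not help, because the wrong quantity is being estimated.

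**Working it through.** **1. The plan's own figure.** Inputs from section 2.6.1: expected rate p = 0.80, distance to the lower limit d = 0.15, one-sided 95%. Then n = z² p(1 − p)/d² = 1.645² × 0.16/0.0225 = 19.24, rounded up to 20. Adding 2 drop-outs gives 22. The stated sample size reproduces. It concerns the preference rate and is not in question here; it only fixes how many patients are available for a healing contrast.

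**2. Exposure by randomised group.**

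| Time | Cap first | Film first | What the groups differ in |
|---|---|---|---|
| Day 14 | 14 days cap | 14 days film | device |
| Day 28 | 14 cap, then 14 film | 14 film, then 14 cap | order only |
| 4 months | as day 28, then chosen device, then film if unhealed at day 42 | the same | order, with self-chosen treatment mixed in |

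**3. What each comparison estimates.** Let t1 be the cap-minus-film effect on healing in weeks 0–2 and t2 the same in weeks 2–4, with effects additive. Let m be the mean result at the time in question under film throughout.

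- Day 14: (m + t1) − m = t1, the device effect.
- Day 28: (m + t1) − (m + t2) = t1 − t2, an order effect.

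**4. Numerical check.** Simulation with 11 v 11 (1:1 assumed), SD 1 at each time, 20,000 runs, two-sided t test at 0.05:

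| t1 | t2 | Day-14 difference (rejection) | Day-28 difference (rejection) |
|---|---|---|---|
| 1 | 1 | 1.00 (61%) | 0.00 (5.2%) |
| 1 | 0.5 | 1.00 (61%) | 0.50 (20%) |
| 1 | 0 | 1.00 (61%) | 1.00 (61%) |
| 0.5 | 1 | 0.50 (20%) | −0.50 (20%) |

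The day-28 difference equals the early device effect only if the device has no effect in the second fortnight. With equal effects it is zero and the test rejects at about its nominal level. With a larger late effect the better device looks worse.

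**5. What day 14 could deliver.** The allocation ratio and the SD of the healing measures are not given, so results are in SD units under an assumed 1:1 split. Detectable difference by normal approximation, two-sided 5%, 80% power: (1.960 + 0.842) × √(2/n).

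| Patients per group | Detectable (normal) | Detectable (t test) | Power for 0.5 SD (t test) | 95% CI half-width, 1.960 × √(2/n) |
|---|---|---|---|---|
| 11 | 1.19 SD | 1.26 SD | 20% | 0.84 SD |
| 10 | 1.25 SD | 1.32 SD | 19% | 0.88 SD |

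**The case against.** **The healing measures may be meant as description.** Section 2.1 attaches a comparison with film to safety, quality of life and unplanned dressing changes, but not to the healing sentence. The abstract also states an aim of describing the clinical course, and section 2.8 makes all secondary endpoints exploratory. This largely stands: 28 days and 4 months are sensible times for description. But these endpoints then cannot carry the efficacy wording. Exploratory status excuses low power, not a contrast that estimates something else.

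**The timing phrase may govern tissue growth only.** The grammar allows this. Re-epithelialisation would then have no stated time, and the point still holds for tissue growth and the 4-month measures.

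**Day-14 data may already be planned.** Section 2.5 says "At each visit the dressing or, when applicable, the exposed finger is photographed from all perspectives", with digital analysis and 3-D volume modelling over time. The images could therefore exist, and the full protocol or SAP may use them. That makes the remedy cheap. The endpoint times and the efficacy wording are nevertheless fixed in the article, so the mismatch is not an omission.

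**A crossover analysis could recover the device effect.** Comparing growth in days 0–14 with growth in days 14–28 is arithmetically possible, but it needs no carry-over, which is implausible in a healing wound.

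**Stronger readings that the documents do not support.**

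- A reader might infer that day 14 is the trial's only randomised device comparison. It is not. Quality of life is scored at each visit and unplanned dressing changes can be counted per period. The randomised order allows a within-patient comparison of both if carry-over is negligible, and section 2.8 lists paired tests.
- A reader might infer that the day-28 difference must be zero. That needs equal device effects in both fortnights.
- A reader might expect an analysis by chosen device. None is proposed.
- A reader might compute unequal exposure to day 42, 14 + 0.8 × 14 = 25.2 days of cap against 14 + 0.2 × 14 = 16.8 of film, a ratio of 1.5. At an 80% cap choice this is an upper bound, because it assumes every patient needs occlusion to day 42. The ratio tends to 1 if wounds close by day 28. The article states no event-count window to which it would apply.

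**Conclusion.** The point holds for cumulative, irreversible healing outcomes: re-epithelialisation, tissue growth and the 4-month functional measures. At the stated times the randomised groups differ by device order, so a cap-versus-film healing effect is not identified, and the efficacy and effectiveness wording in the abstract and Introduction is not supported by these endpoints. The day-28 group difference is t1 − t2. It ranged from 1.00 to −0.50 SD in the cases examined, although the cap was beneficial in at least one fortnight in each and harmful in none. This rests on an additive model; the SD-unit figures also assume 1:1 allocation.

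The finding does not reach the primary preference endpoint, the sample size, or outcomes recorded within each period. It is an inexpensive improvement worth making, not a fault in the trial's main question.

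**What to change.** 1. Name day 14, before the device exchange, as the exploratory between-group time point for re-epithelialised area and 3-D volume. Compare cap-first with film-first, adjusted for the initial defect, and report the estimate with its confidence interval.
2. State that the exposed finger is photographed at that visit. The general rule allows a photograph of the dressing instead, but section 2.5 already has both devices exchanged on that day.
3. Label the 28-day and 4-month healing and functional results as whole-cohort description or as a comparison of sequences.
4. Narrow the efficacy and effectiveness wording in the abstract and Introduction to match.

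The cost is some extra image analysis and changes of wording. Treatment, visits, sample size and primary endpoint stay as they are. The price is a narrower efficacy claim resting on an imprecise contrast, which should be presented as estimation for planning and not as a test of the cap.

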**Figure 1 F1:**
[figure not shown]
Pseudo-cross-over study design of this study.

### Treatment group

2.2

The silicone finger cap consists of a thin and soft silicone shaft that surrounds the basis of the finger and provides the semiocclusive seal without the need for additional adhesives. It is thus a further development of conventional occlusive means such as self-adhesive films or fingers of sterile rubber gloves. The finger cap forms a protected chamber of more rigid silicone around the distal phalanx that is close to the original, anatomical form, and size of the fingertip. The more rigid silicone is continued in a narrow bar all the way to the base of the finger cap thus splinting the injured finger enough to care for undisturbed healing while allowing some movement in all finger joints. A reservoir for excess wound fluid is connected to the wound chamber by capillaries, thus enabling free diffusion in between the wound and the reservoir (Fig. 2). This reservoir can be punctured with a regular injection needle. The used medical silicone Dragon Skin Series Part A&B (KauPo, Spaichingen, Germany), Silastic Q7-4720 Biomedical Grade ETR Elastomer and Silastic Q7-4765 Biomedical Grade ETR Elastomer (Dow Corning, Midland, TX) is permeable to oxygen to some extent but impermeable to water vapor. For this series all finger caps are individually handcrafted by Orthopedic and Rehabilitation Engineering Dresden (GmbH), Dresden, Germany, the sponsor of this clinical trial. Besides, the sponsor office was committed to the Coordinating Centre for Clinical Trials Dresden.

**Figure 2 F2:**
[figure not shown]
Novel silicone finger cap. (A) dorsal view, (B) sagittal view: (1) apex, (2) protective cap of rigid silicone, (3) reservoir, (4) capillary, (5) chamber for injured finger, (6) thin and soft silicone, (7) incorporated splint of more rigid silicone, and (8) base.

### Control group

2.3

In our control group, we start the treatment with a self-adhesive polyurethane film dressing as it is used in most centers as standard therapy.^[4,8,13,15–18]^ Opsite Flexigrid transparent dressing (Smith & Nephew Medical Limited, Hull, England) is a transparent film dressing, comprised of a polyurethane film with acrylic adhesive. It is Communauté Européenne (certification mark indicating conformity with European legislation)-certified and it is classified according to the European classification of medical devices in group IIa.

### Inclusion and exclusion criteria

2.4

The participants are recruited by trained surgeons in the Emergency Department of the University Hospital Carl Gustav Carus at the Technische Universität Dresden, Germany. We include male and female patients older than 2 years with full skin substance defects distal to the distal interphalangeal joint unsuitable for primary surgical closure without further substance loss. No more than 5 fingers per patient may be injured. Patients must have a circumference of the proximal phalanx in between 3.0 and 9.0 cm. In addition, a signed written informed consent must exist.

We exclude the participation of any patient with known hypersensitivity against medical silicone or self-adhesive films. Further exclusion criteria are bony injuries requiring a surgical intervention, bite injuries, or chronic dermatological disorders of the hand. Furthermore, intake of medications affecting wound healing, such as systemic (noninhalative) glucocorticoids, immunosuppressive, or blood-thinning medications are exclusion criteria. Patients with a known wound healing disorder are also excluded from this clinical trial. In addition, ongoing or recently finished chemotherapy, immunodeficiencies or diabetes mellitus, are exclusion criteria. In accordance to §20 of the German Medical Device Act, pregnant or breastfeeding women, as well as any women, when a pregnancy at the beginning or during the course of the study cannot be ruled out (ie, not postmenopausal, no bi-lateral oophorectomy or hysterectomy, no contraceptive method with pearl index less than 1%, no sexual abstinence, or partner with vasectomy) will have to be excluded. Beyond that, patients who are suffering from an addiction or other diseases, which do not allow them to assess the entity, scope, and possible consequences of this clinical trial are also excluded. The same applies for patients who are not cooperative or who already participated in other clinical trials within the last 4 weeks.

